## Abstract

**Background:**

Poor feeding practices during infancy contribute to obesity risk. As infants transition from human milk and/or formula-based diets to solid foods, these practices interfere with infant feeding self-regulation and healthy growth patterns. Compared with other socioeconomic groups, lower-income mothers are more likely to experience difficulty feeding their infants. This may include misinterpreting feeding cues and using less-than-optimal feeding styles and practices, such as pressuring infants during mealtimes and prematurely introducing solid food and sweetened beverages. The Healthy Babies trial aims to determine the efficacy of a community-based randomized controlled trial of an in-home intervention with economically and educationally disadvantaged mother-infant dyads. The educational intervention is being conducted during the infant's first 6 months of life to promote healthy transition to solids during their first year and is based on the theory of planned behavior.

**Methods/Design:**

We will describe our study protocol for a multisite randomized control trial being conducted in Colorado and Michigan with an anticipated sample of 372 economically and educationally disadvantaged African American, Hispanic, and Caucasian mothers with infants. Participants are being recruited by county community agency staff. Participants are randomly assigned to the intervention or the control group. The intervention consists of six in-home visits by a trained paraprofessional instructor followed by three reinforcement telephone contacts when the baby is 6, 8, and 10 months old. Main maternal outcomes include a) maternal responsiveness, b) feeding style, and c) feeding practices. Main infant outcome is infant growth pattern. All measures occur at baseline and when the infant is 6 and 12 months old.

**Discussion:**

If this project is successful, the expected outcomes will address whether the home-based early nutrition education intervention is effective in helping mothers develop healthy infant feeding practices that contribute to improving infant health and development and reducing the risk of early-onset childhood obesity.

**Trial Registration:**

Current Controlled Trials ACTRN126100000415000

## Background

The Institute of Medicine and Healthy People 2010 [1] identify childhood obesity as a serious nationwide health problem requiring urgent attention in the United States. An estimated 10 million children are overweight, a number that has doubled in the past 20 years [2], with the prevalence of overweight in infancy increasing from 11% to 17% [3]. Obesity is more prevalent in lower-income and minority children, placing them at increased risk for later health problems, such as hypertension, cardiovascular disease, and type II diabetes [4].

Although the causes of obesity among children are multilayered, data suggest that by toddlerhood, many children are at risk because of overeating. Thus, preventive feeding interventions are especially necessary during age-appropriate transition to solid foods. Mothers' misinterpretation of infant feeding cues, the use of controlling feeding styles, and poor feeding practices can affect infants' ability to regulate food intake [5]. Although mothers have some knowledge about infant nutrition and feeding cues as infants transition from human milk/formula-based diets to solid foods, they continue to rely on inappropriate indicators of satiation, such as infants' sleeping through the night and advice from extended family members [6]. Our study focuses on the promotion of healthy infant feeding practices in reducing the risk of early onset of childhood obesity.

Learning to feed effectively early on has been shown to help mothers develop positive feeding relationships with their infants and promote infant feeding self-regulation and normative growth patterns. Maternal responsiveness, maternal feeding style, and appropriate feeding practices are three critical components in the development of infant feeding self-regulation [7]. From a prevention perspective, maternal relationship and skill-building intervention approaches that target maternal responsiveness, feeding styles, and feeding practices must be evaluated for feasibility, effectiveness, and sustainability to reduce the risk of childhood obesity. To date, we have identified only one intervention study [8] designed to improve feeding behaviors of infants transitioning from human milk or formula to solid foods delivered by trained community nurses.

The Healthy Babies (HB) intervention we have designed addresses three major gaps that exist in infant feeding intervention research. First, few studies have been tailored to assist mothers of lower incomes with transitioning their infants to solid foods. Second, studies have historically focused on the feeding of preschoolers and older children rather than infants. Third, most existing interventions use models focused on nutritional knowledge enhancement without a relationship-skill component. Increasing maternal knowledge without addressing the family and cultural context and practices through which mothers apply this knowledge does not provide mothers with the relationship skills and strategies to change and improve maternal responsiveness, feeding styles, and feeding practices.

### Aims and Hypotheses

The aim of the study is to compare the effect of a home-based intervention for economically and educationally disadvantaged mothers of infants, 4 months of age or younger, versus standard nutrition education on maternal responsiveness, feeding style, and feeding practices.

Mothers with infants under 4 months of age will receive one of the two following interventions:

1) In- home HB intervention delivered by a trained paraprofessional instructor [a person who is appropriately trained and supervised in providing nutrition education instruction to families] prior to when the infant is 6 months of age promoting healthy feeding practices and enhanced mother-infant interaction, plus three reinforcing telephone contacts when the baby is 6, 8, and 10 months old.

2) Traditional nutrition education (EFNEP, the Expanded Food and Nutrition Education Program, a standard nutrition education curriculum offered in each state through county Cooperative Extension Service programs) consisting of six in-home nutrition education lessons delivered by a paraprofessional instructor prior to when the infant is 6 months of age that does not include extensive content on infant-centered feeding.

We hypothesize that the in-home HB intervention relative to usual nutrition education will be associated with:

• An increase in maternal responsiveness

• An increase in healthy maternal feeding style

• An increase in healthy age-appropriate infant feeding practices

• Healthy, age-appropriate infant growth patterns of weight and length

• Mothers' satisfaction with the HB intervention

• Feasibility in a community-based setting in the United States

## Methods/Design

### Overall study design

The design of this study is a randomized, experimental, short-term, longitudinal controlled trial (RCT) with a convenience sample of economically and educationally disadvantaged mothers of infants living in Colorado and Michigan. Participants are randomly assigned to the HB intervention or a control group with a goal of N = 139 participants per group by Time 3 data collection. There are three assessment periods: baseline (Time 1), when the infant is 6 months of age (Time 2), and when the infant is 12 months of age (Time 3). The United States Department of Agriculture (USDA) has funded this project for 3 years, making this multi-state collaboration between Michigan and Colorado possible.

### Development of the intervention

The HB intervention was developed and refined based on a pilot project, the Infant Feeding Series (TIFS) [9,10], that provided initial evidence of lower-income mothers delaying the early introduction of solid foods until the infant was between 4 and 6 months of age as recommended by the American Academy of Pediatrics. HB addresses core infant nutrition concepts but also focuses on: a) infant normative growth and development (e.g., infant cues, temperament, behavioral states); b) mother-infant feeding relationship skill-building (i.e., maternal responsiveness); support for mothers in creating their own infant feeding plans); and d) skills and strategies for implementing and sustaining their feeding plans and new feeding practices and styles. The curriculum focuses on a specific concern that emerged from our previous work: that economically and educationally disadvantaged mothers need help in delaying the early introduction of solids to their infants [10]. The Theory of Planned Behavior (TPB) [11] guided our understanding of maternal behaviors in the parent-infant feeding interactions and decisions. The TPB is commonly used to predict health-related behavioral intentions and behaviors. Organizing principles of the TPB provided the basis for the development of the HB lessons and the following framework for their delivery [12]. Staff members in Cooperative Extension Service programs in both states reviewed the lessons for appropriateness and feasibility.

### Participants and recruitment

Participants with the following characteristics are being recruited: low-income (≤ 185% federal poverty level in the US and eligible for federal food assistance programs); 18 years of age or over; mothers of infants less than 4 months of age who have not started solid foods; a primary caregiver of the infant, and neither mother nor infant has a diagnosed eating, physical, or chronic health problem. Mother-infant dyads are targeted for recruitment from local community programs, such as the Special Food Supplemental Nutrition Program for Women, Infants, and Children (WIC), a federal assistance program of the Food and Nutrition Service of the USDA, food pantries, hospitals, physicians' offices, and immunization clinics. Staff from these programs provide information about the study and encourage mothers with infants to enroll in the project.

Once eligibility is established, families are contacted for the initial data collection home visit where written informed consent is obtained. Newly recruited participants are not previously enrolled in EFNEP. We have obtained ethical approval to conduct this trial from the University Committee on Research Involving Human Subjects from Michigan State University and the Institutional Review Board for Human Subjects from Colorado State University. Informed consent for voluntary participation is obtained prior to commencement in the study.

### Randomization

Following consent and baseline data collection, mothers are randomized into either the HB or control group. This is done via computer minimization procedure, balancing groups with respect to the county recruitment locations. According to CONSORT guidelines [13], allocation concealment is used to prevent participants, data collectors, and paraprofessionals from knowing which group the participants will be assigned. Only after enrollment in the program do researchers assign participants into intervention or control groups. The assignment of groups is withheld from data collectors throughout the entire length of the study. Separate paraprofessional instructors deliver either the HB intervention or the traditional nutrition education; separate individuals who are not paraprofessional instructors are trained as data collectors in each county to do the in-home data collection at each time period.

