### Intervention group

The Healthy Babies intervention consists of six in-home lessons taught by a trained paraprofessional instructor followed by three reinforcement telephone calls. Each lesson (60 minutes in length) is designed to promote the development of healthy infant eating and incorporates research-based information, opportunities for mothers to develop and practice skills, and a discussion of strategies to overcome challenges and problem-solving techniques. The three telephone contacts, about 5 minutes in length, made at 6, 8, and 10 months, are used to reinforce key concepts in the lessons after conclusion of the intervention to maintain effects and sustain contacts with participants to improve retention.

Six lessons have been identified as the number of lessons that best balance likelihood of completion by participants and likelihood of intervention impact. Six lessons have been found to produce behavioral change [14] and represent sufficient time to build a supportive relationship with the individual mothers.

During the six lessons, mothers will engage in activities in support of lesson goals. Intervention strategies focusing on feeding practices will include modification of the feeding environment (e.g., turning the TV off during feeding). An animated DVD, which includes actual footage of infant and parent behaviors, will be used to demonstrate infant temperament traits.

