### Control group

The control group families receive the usual care provided by ENFEP. These families are newly enrolled into EFNEP as part of the HB study and have not received home visitation previously. The control lessons are delivered in a similar manner as the HB lessons, such that a paraprofessional instructor provides six lessons during an in-home visit, which each lesson lasting approximately 60 minutes. However, the control lessons focus solely on nutrition and the major food groups and do not include extensive content on infant-centered feeding. Paraprofessional instructors who provide the lessons for the control group families are different from the instructors who provide the HB lessons to prevent cross-contamination between the two groups.

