### Sample size, power calculations, and data analysis

#### Sample size and power calculations

A convenience sample of 394 mother-infant dyads (186 each per intervention and control group) is anticipated. Effect sizes were estimated from similar available data and are calculated to be conservative to avoid Type II errors. To assess differences in groups cross-sectionally, the maternal Nursing Child Assessment Satellite Training (NCAST) data were used with a reported an effect size *(d*) of .35. The minimal detectable effect size (MDES) with power of .80 with an alpha level of 5% for 2-tailed tests is .33 expressed as Cohen's d. Effect sizes exceeding .30 are deemed more likely to reach clinical significance. We used normative data from the NCAST database containing data from 431 African American women to provide examples of projected changes in outcomes that, if produced by the HB intervention, will be detected as statistically significant.

The MDES was calculated for the pair-wise group differences using an approach described by Rochon [20]. We used H3 type of hypothesis since the model contains group-by-time interaction, and the standardized MDES was approximately 0.4. That is, if the minimum difference between groups divided by the maximum standard deviation across two time points is equal to 0.4 or greater, then the treatment difference inconsistent over time will be detected as statistically significant with power .80 and alpha = .05 for 2-tailed tests. A 70% to 75% completion rate is typical for nutrition education. These factors have led us to propose a sample size for analysis by Time 3 of 278 mother-infant dyads, 139 per group after accounting for estimated attrition. Including oversampling to accommodate a conservative estimate of 25% attrition after 1 year, the final sample size to be enrolled is 372, 186 per group and per state (in each state, 93 mothers and infants will be recruited for each group).

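### The detectable effect of .33 makes no allowance for instructor clustering, although each arm has its own instructors, so it is attained only if the instructor ICC is zero

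*Protocol article*

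**What the plan says.** Mothers are randomized individually, by minimization on county of recruitment (protocol article, Randomization). Delivery is then split by arm: "Separate paraprofessional instructors deliver either the HB intervention or the traditional nutrition education". The Control group section confirms this and gives avoidance of contamination as the reason: "Paraprofessional instructors who provide the lessons for the control group families are different from the instructors who provide the HB lessons". Both arms receive six home lessons of about an hour each. The Intervention group section justifies that number partly because six lessons "represent sufficient time to build a supportive relationship with the individual mothers".

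The section on sample size and power calculations states: "The minimal detectable effect size (MDES) with power of .80 with an alpha level of 5% for 2-tailed tests is .33", in units of Cohen's d. It cites an effect of d = .35 from similar data, and a second detectable effect of about 0.4 for the group-by-time hypothesis. The analysed sample is 278 dyads, 139 per group, raised to 372 enrolled (186 per group) for 25% attrition. The section mentions no number of instructors, ICC or design effect.

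The Data analysis section names MANOVA, chi-square tests and generalized linear mixed models for comparing the groups at baseline. It allows covariate adjustment if the groups differ, and says that the primary analysis is by intention to treat. It states no model for the outcomes.

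**The concern.** No instructor teaches in both arms, so differences between instructors do not cancel in the arm comparison. They add to its variance. Minimization on county cannot balance them, because instructor is determined by arm. Keeping data collectors unaware of allocation does not help either, since the correlation arises in delivery and not in measurement. The article itself relies on the relationship between instructor and mother as part of how the lessons work, so zero variance between instructors is a strong assumption.

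Two things are at stake. First, the sample size section claims a detectable effect that the design may not deliver. Second, if the outcome analysis also left instructor out, a few unusually good or poor instructors in one arm could pass for an intervention effect.

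**Working it through.** **Inputs from the article (sample size section):** two-sided alpha .05, power .80, 139 analysed per group, stated detectable effect (MDES) .33, cited effect d = .35, attrition 25%.

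**Inputs assumed, because the article does not give them:** k instructors per arm and the instructor ICC. The same ICC and equal caseloads m = 139/k are taken in both arms.

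**Step 1: reproduce the plan's figure.** Under independence, MDES = (1.960 + 0.842) × sqrt(2/n).
- n = 139: 2.8016 × sqrt(2/139) = .336 (.337 with the t distribution). Power at d = .33 is 78.6%.
- n = 186: .291. n = 197 (half of the 394 also printed in that section): .282. One-sided at n = 139: .298.

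Of these, only 139 per group, two-sided, with design effect 1 comes close to .33. Enrolment is 139/.75 = 185.3, hence 186 per group and 372 in total, so attrition is the only inflation.

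**Step 2: margin.** With design effect DE = 1 + (m − 1) × ICC, the MDES becomes .336 × sqrt(DE). It exceeds the cited .35 once DE > (.35/.336)² ≈ 1.085. With 10 instructors per arm (m = 13.9), that is ICC ≈ .085/12.9 ≈ .007.

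**Step 3: three scenarios.** For a test that accounts for clustering, power at d = .35 is Φ(.35/sqrt(2·DE/139) − 1.96). For a test that ignores it, the actual type I error is 2 × (1 − Φ(1.96/sqrt(DE))), and power is Φ((.35/sqrt(2/139) − 1.96)/sqrt(DE)).

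| k per arm, ICC | DE | MDES | Power at .35, clustering accounted for | Type I error, clustering ignored | Power at .35, clustering ignored |
|---|---|---|---|---|---|
| independence | 1 | .336 | 83% | 5% | 83% |
| 12, .01 | 1 + 10.58 × .01 = 1.11 | .35 | 79% | 6% | 82% |
| 8, .02 | 1 + 16.38 × .02 = 1.33 | .39 | 72% | 9% | 80% |
| 6, .05 | 1 + 22.17 × .05 = 2.11 | .49 | 52% | 18% | 75% |

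These are normal approximations. With a t reference on 2(k − 1) degrees of freedom, the three MDES values become .37, .42 and .54, so power for the clustering-adjusted test is somewhat lower than shown.

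**Step 4: wider range.** Over 4 to 20 instructors per arm and ICC .01 to .10 (normal approximation), the MDES runs from .35 (20 per arm, ICC .01) to .70 (4 per arm, ICC .10).

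The group-by-time figure of about 0.4 cannot be reproduced, because no within-subject correlation is given. No clustering allowance is stated for it either.

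**The case against.** The strongest objection concerns the analysis. A reader might infer that the plan analyses mothers as independent, with mixed models kept only as a fallback for non-normal data, and so conclude that its standard errors are too small. The article does not support this. The sentence naming MANOVA, chi-square tests and mixed models is about the baseline comparison. The outcome model is not stated, and its random-effects structure may stand in a full protocol or analysis plan that is not shown. An instructor term is neither included nor excluded. This objection stands, so the type I error figures apply only if that term is omitted.

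A second tempting reading is that inflated type I error and the full loss of power occur together. They do not, because they belong to different tests. If clustering is ignored, type I error is 6%, 9% and 18%, but power at d = .35 is still about 82%, 80% and 75%. The figures of 79%, 72% and 52% belong to a test that accounts for clustering.

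Third, the size rests on assumed values. In the mildest scenario the MDES only reaches the cited .35. County is balanced by minimization, so only instructor variance within county and arm matters, and the ICC should be read that way. This limits what can be said about size but leaves the direction unchanged: any positive ICC moves the MDES up.

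The power calculation itself is not something left to another document. It is printed, and it matches design effect 1.

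**Conclusion.** The point holds for the power statement. Instructors are nested within arm, the stated MDES is the independent-observations value, and it is attained only with an instructor ICC of zero. This does not depend on the unseen outcome model. If that model includes instructor, the printed MDES does not match it. If it does not, the test does not hold its 5% level. Either way, with a positive ICC, the combination of 80% power, 5% alpha and .33 is not delivered.

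The size is uncertain because the article gives neither instructor numbers nor an ICC. A plausible reading runs from negligible (many instructors, ICC near .01) to serious (six per arm, ICC .05). The documents do not support saying that the trial's standard errors are wrong, or that any one of these scenarios applies.

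**What to change.** 1. Record the assigned instructor for each dyad. Assigned rather than actual instructor respects intention to treat. Do this while lessons are being delivered, since later reconstruction may be unreliable.
2. In the outcome model, include instructor nested within arm as a random effect, with county as a fixed effect and Satterthwaite or Kenward-Roger degrees of freedom. If the full analysis plan already does this, the article needs only to say so.
3. In the sample size section, give the number of instructors per arm and restate the MDES with DE = 1 + (m − 1) × ICC over a stated ICC range.

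The cost is one variable, one model term and a less favourable MDES. The change gives valid inference and an honest figure but does not recover lost power. For scale, keeping .336 with caseloads of 13.9 (the 10-per-arm case) and ICC .05 would need 278 × 1.645/.75, about 610 enrolled instead of 372, with instructors added in proportion.
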